#### PTSD Assessment

This study includes an assessment of PTSD as a secondary measure. It aims to evaluate the potential impact of PTSD on the primary outcome of fatigue and provide a better characterization of the study population. Although previous PTSD to COVID-19 infection is an exclusion criterion, some participants may still have experienced PTSD symptoms after their COVID-19 infection, so evaluating the prevalence and severity of these symptoms in the study population could be relevant.

Given that the “gold standard” clinician-administered, semistructured psychiatric interviews to diagnose PTSD symptoms were not feasible during the workload of the COVID-19 follow-up clinic, we chose the patient-reported outcome instrument PTSS-14. This scale was developed based on the Diagnostic and Statistical Manual of Mental Disorders, Third Edition, Revised (DSM-III-R) criteria for PTSD and subsequently validated for patients following intensive care [38]. Patients were asked to assess the frequency of 10 common PTSD symptoms on a 7-point Likert scale from 1 (never) to 7 (always). Item scores were summed up to a total score (ranging from 10 to 70). A total score above 35 was suggested to indicate clinically relevant PTSD symptoms. A similar 14-item version of PTSS was later developed to reflect the changes in the fourth edition of the DSM (DSM-IV), where a cutoff value of 45 indicated presumable PTSD [39]. We modified the latter to include COVID-19 patients—whenever the term “intensive care unit (ICU)” appeared, we substituted it with “COVID-19.” We applied the same diagnostic cutoff to this adapted scale.

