Fatigue, a primary persistent symptom of long COVID, has been reported in 10% to 70% of patients [16-19]. It is defined as “a decrease in physical or mental performance that results from changes in central, psychological, or peripheral factors due to the COVID-19 disease” [20]. Thus, post–COVID-19 fatigue depends on conditional and psychophysiological factors comprising the individual’s task, environment, physical, and mental capacity, as well as the disease’s central, psychological, and peripheral aspects [20].

While fatigue is not traditionally considered a neuropsychiatric disorder, it can be a symptom of many mental health conditions, such as depression, anxiety, and posttraumatic stress disorder (PTSD) [21,22]. Therefore, it is often included in discussions of mental health symptoms in post–COVID-19 syndrome [23]. The term “neuropsychiatric” often refers to a wide range of disorders affecting the brain and mental health. In contrast, “neuropsychological” refers to studying the relationship between brain function and behavior [24]. The primary focus of this study is on psychiatric symptoms, particularly depression and anxiety. However, we will also investigate PTSD, which is a neuropsychiatric disorder involving both neurological and psychiatric aspects. In addition, the health-related quality of life (HRQoL) assessment includes a section that evaluates aspects related to anxiety and depression. While not designed for diagnosing psychiatric disorders, this assessment can help gauge how these symptoms affect a person’s overall quality of life, making it more of a general health assessment.

The current literature on long COVID and its mental sequelae has relied on self-reported symptoms through questionnaires administered either in-person or through telephone interviews to comply with public health guidelines. However, the correlation between these self-reported symptoms needs to be clarified. There is an obvious need to accurately characterize the mental sequelae of COVID-19 and the risk factors associated with these outcomes.

This study aims to quantify the degree of physical and psychological fatigue in patients post COVID-19 and assess the correlation of fatigue with other mental sequelae—particularly depression, anxiety, and PTSD. Furthermore, we aim to explore its impact on HRQoL.

Our research questions for this study are outlined in Textbox 1.

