Research questions of the study.Research Question 1 (primary outcome):Do patients with long COVID who experience depression and/or anxiety symptoms have a higher prevalence of fatigue?Research questions 2 to 4 (secondary outcomes):Is there a correlation between the type of fatigue and depression and/or anxiety symptoms among patients post COVID-19?Is there a correlation between fatigue and the presence of PTSD symptoms in patients post COVID-19?Do patients with fatigue associated with mental health disorders have a lower health-related quality of life (HRQoL) after COVID-19?

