### Data Collection

Data collection will take place during appointments at the long COVID follow-up clinics in all participating hospitals. Qualified clinical study staff will gather the data using a clinical research form (CRF) (Multimedia Appendix 1). These individuals comprise health care professionals, such as nurses, clinical research coordinators, and health care experts who have received appropriate training and have the necessary expertise to conduct data collection and assessments in a clinical research setting. Their training ensures adherence to research protocols and ethical guidelines, guaranteeing accurate and consistent data gathering during clinical appointments. Two months after hospital discharge, we will mail all patients a letter offering a follow-up consultation in the outpatient clinic. Patients who agree to attend will be offered 2 appointments, consisting of an anamnesis and a physical examination, and given several self-administered tests in the waiting room. We will allocate 15 minutes for the questionnaire completion in the waiting room. In the first visit (T1, 3 months), the following data will be additionally collected: demographic characteristics like age, sex, and BMI (kg/m^2^); each participant’s medical history, such as the date of the first positive COVID-19 test (PCR or antigen) and smoking, alcohol, and drug consumption status; comorbidities and usual medication intake; and screening of symptoms and severity of the acute disease. Data collection in the second visit (T2, 6 months) will include post–COVID-19 symptoms, the Chalder Fatigue Scale [26] (CFQ-11), the Hospital Anxiety and Depression Scale (HADS) [27], the 14-item Posttraumatic Stress Scale (PTSS-14) adapted to COVID-19, and the EQ-5D [28] questionnaire.

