The 5 phases of the statistical analyses carried out in this study.Phase 1: Characterization of the patient sample1.1. Sociodemographic analysis of the variables collected at T1 and the variables from the surveyed instruments at T2. This involves descriptive analysis, both univariate and bivariate, which will be differentiated by:1.1.1. Quantitative variables: mean and SD, coefficient of variation, and median and IQR1.1.2. Qualitative variables (nominal and ordinal categorical): analysis of distributions through absolute and relative frequencies, including absolute and relative accumulated frequencies1.1.3. Quantitative variables will be reported alongside appropriate tests for normal distribution to ensure the accuracy and validity of our statistical analyses.1.2. Bivariate and descriptive analysis using 2D tables will be calculated for all qualitative variables belonging to T1 with all instrument scores collected at T2: Chalder Fatigue Scale (CFQ-11), Hospital Anxiety and Depression Scale (HADS), 14-item Posttraumatic Stress Scale (PTSS-14) adapted to COVID -19, and EQ- 5D plus recorded COVID-19 symptoms. The previous points will be reiterated in this bivariate context, utilizing the computational aid of split->file categorical variables in situations where one variable is metric and the other is categorical.1.3. Internal consistency and reliability analysis of the T2 instruments: calculation of the Cronbach alpha (general and partial) for all ordinal items and item subgroups differentiated by the subscales defined by the respective authorsPhase 2: Determination of fatigue incidence caused by long COVID and its relationship with T1 and T2 variables2.1. Procedures for determining fatigue cutoff points in this cohort of patients:2.1.1. Bivariate analysis using optimal binning procedures for categorical variables (age class, sex, and BMI) with the total fatigue score, as well as partial scores of physical and psychological fatigue2.1.2. Multivariate analysis by constructing models in the format of decision trees via the CHAID (chi-square automatic interaction detection) algorithm [41], with total and partial fatigue scores as dependent variables2.2. Inferential analysis based on variables resulting from 2.1.1 and/or 2.1.2, considering the complexity of variables in T1 and T2:2.2.1. (1) Chi-Square tests to capture the association of categorical variables; (2) Shapiro-Wilk tests to verify the distribution of quantitative variables; (3) tests for comparing 2 or more population means: parametric analysis of variance (ANOVA) test and nonparametric (Kruskal-Wallis) test; and (4) correlation tests (Spearman or Pearson) to verify the degree of association between T2 instrument scalesPhase 3: Determination of patient groups based on fatigue differentiation3.1. Conducting classification analysis using clustering techniques, specifically the 2-step cluster analysis, to explore variables with greater power in differentiating groups of patientsPhase 4: Exploration of the best combination of T1 and T2 variables capable of discriminating patient fatigue levels through a discriminant multivariate analysisPhase 5: Investigation of the association between phase 3 groups and all T2 instrument scales using chi-square association tests

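### The protocol wants the impact of PTSD on fatigue, but its planned tests give only an unadjusted association that cannot be told apart from the depression and anxiety link

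*Protocol article*

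**What the plan says.** The PTSD Assessment section gives the purpose of the PTSS-14: "It aims to evaluate the potential impact of PTSD on the primary outcome of fatigue". It adds a second purpose, describing the study population better. Research question 3 in Textbox 1 (Introduction) is milder: "Is there a correlation between fatigue and the presence of PTSD symptoms in patients post COVID-19".

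In Textbox 2 (Statistical Analyses), step 2.2.1 lists chi-square tests, ANOVA or Kruskal-Wallis, and "correlation tests (Spearman or Pearson) to verify the degree of association between T2 instrument" scales. Phase 5 is "Investigation of the association between phase 3 groups and all T2 instrument scales using chi-square association tests". All of these relate two variables at a time.

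Two steps use several variables together. Step 2.1.2, listed under procedures for finding fatigue cutoffs, is "Multivariate analysis by constructing models in the format of decision trees via the CHAID (chi-square automatic interaction detection) algorithm", with fatigue scores as dependent variables. Phase 4 is an exploratory discriminant analysis of fatigue levels over T1 and T2 variables.

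Under Data Collection, "Data collection in the second visit (T2, 6 months) will include" the CFQ-11 together with "the Hospital Anxiety and Depression Scale (HADS) [27], the 14-item Posttraumatic Stress Scale (PTSS-14) adapted to COVID-19, and the EQ-5D" questionnaire. The Introduction says of fatigue that "it can be a symptom of many mental health conditions, such as depression, anxiety, and posttraumatic stress disorder (PTSD").

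**The concern.** The stated aim is stronger than the analysis. An impact of PTSD on fatigue suggests something PTSD contributes beyond depression and anxiety. The study already expects depression and anxiety to go with fatigue (research question 1), and the Introduction treats fatigue as a possible symptom of all three conditions. If patients with high HADS scores also tend to have high PTSS-14 scores, the PTSS-14 and the CFQ-11 will correlate even when PTSD adds nothing once mood is known.

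A significant correlation could then be reported under the PTSD aim although it restates the finding of research question 1. The scores needed to look at this are collected at the same visit, but no listed analysis uses them for it.

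**Working it through.** **What the listed analyses can deliver**

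| Step in Textbox 2 | Variables at once | PTSD estimate at a given HADS level? |
|---|---|---|
| 2.2.1 chi-square, ANOVA/Kruskal-Wallis, Spearman/Pearson | two | no |
| Phase 5 chi-square | two | no |
| 2.1.2 CHAID | several; predictors not named | none planned; the purpose is cutoffs |
| Phase 4 discriminant analysis | several; PTSS-14 and HADS may both enter | none planned; exploratory |

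**Inputs for the size**

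- N = 200, the number in Power and Sample Size before the allowance for loss to follow-up. It is taken as given. The protocol states no power or precision for research question 3, so there is no figure of its own to reproduce.
- a, the PTSS-14/HADS correlation, and b, the HADS/CFQ-11 correlation. The documents give neither. Assumption: each lies between 0.3 and 0.7.
- Two-sided 5% level (sidedness is not stated; assumed). HADS is treated as a single score.

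**Step 1: induced correlation.** In a linear model with no PTSS-14/CFQ-11 association given HADS, the marginal correlation is r = a × b.

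**Step 2: chance that the pairwise test is significant.** With the Fisher transformation, z = atanh(r) × √(N − 3), where √197 = 14.04. The chance is Φ(z − 1.96) + Φ(−z − 1.96).

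| a | b | r = a × b | z | Pairwise test significant |
|---|---|---|---|---|
| 0.3 | 0.3 | 0.09 | 0.0902 × 14.04 = 1.27 | 24.5% |
| 0.4 | 0.4 | 0.16 | 0.1614 × 14.04 = 2.27 | 62% |
| 0.5 | 0.5 | 0.25 | 0.2554 × 14.04 = 3.58 | 95% |
| 0.6 | 0.5 | 0.30 | 0.3095 × 14.04 = 4.34 | 99% |
| 0.7 | 0.7 | 0.49 | 0.5361 × 14.04 = 7.52 | about 100% |

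**Step 3: check by simulation.** 4,000 runs per setting at N = 200, with no association given HADS and HADS measured without error:

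| a | b | Pairwise test significant | Partial correlation given HADS significant |
|---|---|---|---|
| 0.4 | 0.4 | 62% | 5.0% |
| 0.6 | 0.5 | 99% | 4.6% |
| 0.7 | 0.6 | 100% | 5.3% |

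The two right-hand columns test different hypotheses. The marginal correlation in these settings really is non-zero, so the pairwise rate is not a false-positive rate for research question 3. It shows how often a significant result would appear when PTSD adds nothing beyond HADS.

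**Step 4: precision cost of adjusting.** The standard error of the PTSS-14 coefficient is multiplied by 1/√(1 − a²): 1/√0.75 = 1.15 at a = 0.5 and 1/√0.51 = 1.40 at a = 0.7. This is the collinearity term alone; any fatigue variance explained by HADS offsets part of it.

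**Step 5: effect of error in HADS.** Assume a HADS reliability of 0.8 and observed correlations of 0.6 and 0.5, again with no direct link. The marginal correlation is 0.6 × 0.5 / 0.8 = 0.375. The partial correlation given observed HADS is (0.375 − 0.30)/√(0.64 × 0.75) = 0.108. With N = 200 and one covariate, z = atanh(0.108) × √196 = 1.52, and the adjusted test is significant in about 33% of studies rather than 5%.

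**The case against.** The strongest reply is that the test matches the question. Research question 3 asks about a correlation, the Introduction states the aim as a correlation, and a correlation test is planned. This stands: the pairwise test answers question 3 as worded, and the fault lies in the mismatch with the PTSD Assessment section.

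A reader might infer that PTSD is analysed only pairwise. The documents do not support that, because PTSS-14 and HADS can enter the discriminant analysis together and CHAID is multivariable too. What remains is that neither step is tied to research question 3 or set up to report a HADS-adjusted PTSD estimate.

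A reader might also infer that depression and anxiety will explain the whole association, or that a positive answer to question 3 is nearly certain. Neither can be shown: the protocol gives no inter-scale correlations, and the assumed range starts at about 25%.

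Nor would a HADS-adjusted coefficient be the impact of PTSD. All scales are taken at one visit, so direction is unknown. If PTSD acts on fatigue through depression or anxiety, adjustment removes part of a real effect. Error in HADS leaves some confounding behind (step 5). These points stand and limit how the adjusted result may be described, but they make the unadjusted correlation no better as evidence of impact.

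Finally, the text says potential impact, PTSD is a secondary measure, and a journal article may leave covariates to a fuller plan. That lowers the weight of the point. The aim and the listed tests are nevertheless both stated here, and they do not match.

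**Conclusion.** The point holds as a mismatch between aim and analysis. The planned pairwise tests answer research question 3 but cannot support a statement about the impact of PTSD on fatigue, because they do not separate it from depression and anxiety measured at the same visit.

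With no PTSS-14/fatigue association given HADS, the pairwise test at N = 200 would still be significant in about 25% to 100% of studies. This rests on assumed correlations of 0.3 to 0.7, a linear model and a single HADS score. It is an illustration over a range, not a prediction for this cohort. The change is inexpensive and worth making because it alters what the study can say about PTSD.

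**What to change.** 1. Keep the pairwise correlation as the answer to research question 3.
2. Add one regression of the CFQ-11 total on the PTSS-14 score with the HADS anxiety and HADS depression scores in the same model, or a partial Spearman correlation given both.
3. Report the unadjusted and adjusted estimates side by side, each with a 95% confidence interval. Describe the adjusted one as the association independent of HADS, not as a causal effect.
4. In the PTSD Assessment section, replace *impact* with *association*.

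The cost is one model on data already collected. The downsides are a wider interval for the adjusted estimate (standard error about 1.15 to 1.4 times larger for a PTSS-14/HADS correlation of 0.5 to 0.7), possible over-adjustment if HADS lies on the path from PTSD to fatigue, and residual confounding from error in HADS. The last two should be stated beside the result.

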### Exclusion Criteria

Patients who meet the following criteria will be excluded from participation: (1) preexisting psychiatric disorders diagnosed by a psychiatrist before contracting COVID-19; (2) inability to respond to the questionnaire; (3) concurrent neurological disorders, such as stroke with sequelae, Alzheimer disease, and Parkinson disease; (4) individuals subjected to invasive mechanical ventilation during their COVID-19 infection; or (5) those experiencing persistent fatigue symptoms within the 6 months before SARS-CoV 2 infection.

The study design and inclusion criteria will be reviewed regularly to ensure they align with current best practices and the latest understanding of COVID-19. A patient enrollment flowchart is presented in Figure 1.

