### Limitations

Our study’s limitations include the possibility of sampling bias, as individuals with more severe symptoms of fatigue or other mental health symptoms may be less likely to participate. This possibility could result in underrepresentation and bias within the study’s findings. To minimize this, we will use diverse recruitment methods across multiple sites and collect data on participants’ reasons for declining participation. We will also provide detailed information about the study and its potential benefits to participants while ensuring an ethical and respectful recruitment process sensitive to participants’ health concerns and symptoms.

We also acknowledge the limitations related to our exclusion criteria and use of the CFQ-11, which has yet to undergo specific validation for patients with COVID-19. This recognition underscores the importance of future research endeavors to validate the applicability of the CFQ-11 within this patient population, despite its utilization in prior studies [46-48].

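### The PTSS-14 cutoff of 45, kept unchanged on a reworded scale and called diagnostic, gives an uncalibrated screen-positive rate and not a PTSD frequency

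*Protocol article*

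**What the plan says.** All places are in the protocol article. Under PTSD Assessment, clinician-administered interviews are named as the gold standard, but "semistructured psychiatric interviews to diagnose PTSD symptoms were not feasible" in the follow-up clinic, so a self-report scale is used. The scale first described there was "subsequently validated for patients following intensive care". It has ten symptoms rated 1 to 7, with a threshold above 35. A 14-item version came later, "where a cutoff value of 45 indicated presumable PTSD". The study's own change follows: "We modified the latter to include COVID-19 patients", by putting COVID-19 wherever an item mentioned the ICU. The threshold is kept: "We applied the same diagnostic cutoff to this adapted scale".

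The Abstract lists the prevalence of PTSD symptoms among the secondary outcomes and enrols patients across mild to severe acute illness. Expected Findings adds that nonhospitalized patients are included. Exclusion Criteria removes "individuals subjected to invasive mechanical ventilation during their COVID-19 infection", and the Abstract gives the reason: post-intensive care syndrome is common in that group. Research question 3 relates fatigue to the presence of PTSD symptoms.

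Limitations concedes the "use of the CFQ-11, which has yet to undergo specific validation for patients with COVID-19". It makes no such statement about the adapted PTSS-14.

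**The concern.** Within one paragraph the status of 45 rises from presumable to diagnostic, while the items and the population both change. A threshold carries its sensitivity and specificity only for the instrument and setting in which they were estimated. Here the wording differs, and the patients closest to the named validation setting are partly removed by design. No interview is done against which the threshold could be checked.

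The proportion at 45 could be published as the frequency of PTSD after COVID-19, and the yes/no split could be used to answer research question 3. Phase 5 of the statistical analyses plans chi-square tests of the cluster groups against all instruments from the second visit. Such a test needs categories, and for the PTSS-14 the article adopts only one boundary, 45. A reader of Limitations would not learn that this instrument was altered and not revalidated.

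**Working it through.** **1. What can be reproduced.** The stated range of the ten-symptom scale reproduces: 10 × 1 = 10 and 10 × 7 = 70. If the 14-item version uses the same 1-to-7 scoring (an assumption), its range is 14 to 98. The value 45 cannot be reproduced, because the article gives no sensitivity, specificity or score distribution for it. The article also does not say whether the rule is above 45 or at least 45. For the older scale it does say above 35.

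**2. How an uncalibrated cutoff acts on a proportion.** With true prevalence p, sensitivity Se and specificity Sp:

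- observed rate = p × Se + (1 − p) × (1 − Sp)
- the observed rate exceeds p only if p < (1 − Sp) / [(1 − Sp) + (1 − Se)]

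The sign of the error therefore depends on three quantities, and the article gives none of them for this cohort.

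**3. Range under assumed values.** Every Se/Sp pair is an assumption. The 5.8% is the only PTSD figure in the article. It comes from an external study (Expected Findings), is described there as PTSD symptoms, and serves here only as one possible p. The 10% and 25% are further assumptions.

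| Se / Sp | p = 5.8% | p = 10% | p = 25% | Break-even p |
|---|---|---|---|---|
| 0.90 / 0.90 | 14.6% | 18.0% | 30.0% | 50% |
| 0.80 / 0.95 | 9.4% | 12.5% | 23.8% | 20% |
| 0.70 / 0.97 | 6.9% | 9.7% | 19.8% | 9.1% |
| 0.60 / 0.98 | 5.4% | 7.8% | 16.5% | 4.8% |
| 0.50 / 0.99 | 3.8% | 5.9% | 13.3% | 2.0% |

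First cell: 0.058 × 0.90 + 0.942 × 0.10 = 0.0522 + 0.0942 = 0.146. Last cell of that column: 0.058 × 0.50 + 0.942 × 0.01 = 0.0290 + 0.0094 = 0.038. At p = 5.8% the observed rate is thus between 0.66 and 2.5 times the true one. The first three pairs overcount and the last two undercount. At p = 25% only the first pair overcounts.

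**4. Effect of a shift in scores.** Suppose the threshold had Se 0.85 and Sp 0.90 in its original setting (assumed), and that rewording or the new population moves all scores by −0.5 to +0.5 SD (a normal model for cases and noncases). The observed rate then runs from 7.6% to 25.9% at p = 5.8%, against 14.3% without a shift. At p = 25% it runs from 20.4% to 39.7%, against 28.7%.

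**5. What the planned analyses can and cannot settle.** Phase 1.3 computes Cronbach alpha. That describes internal consistency and says nothing about where a cutoff should lie. Phase 2.2.1(4) correlates the second-visit instrument scales with each other. Both the PTSS-14 and the fatigue scale are second-visit instruments, so that analysis does not depend on 45.

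**The case against.** The strongest defence is that the article is open about what it did. It discloses the rewording, the carried-over threshold and the missing interview, and Limitations concedes that self-report is subjective. The aim is mostly worded as prevalence of PTSD symptoms, and the Discussion says that PTSD is not the primary focus. Research question 3 is phrased as a correlation, the score correlation is already listed, and no planned test is expressly tied to 45. All of this stands, and it keeps the point small. It does not remove the word diagnostic, and it does not give the proportion at 45 a meaning. It also leaves open whether the score or the split answers research question 3.

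A reader might go further and infer that the rate will be too high, with most positives false. Taking 5.8% as true prevalence and pairs from 0.80/0.85 to 0.90/0.95 gives 18.8% down to 9.9% screening positive, which is 3.2 to 1.7 times the truth, with 25% to 53% of positives being true cases. The article does not support that conclusion:

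- It gives no sensitivity or specificity, and those pairs all inflate the count at 5.8%. The table contains pairs that deflate it.
- The 5.8% is an external symptom rate and may itself be a screen-positive rate. This cohort consists of symptomatic clinic attenders. At an assumed 25%, the same two pairs give 31.3% and 26.3%, with 64% and 86% of positives being true cases.
- Even at 5.8%, the better pair leaves 53% of positives as true cases, which is a majority.

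A reader might also call the cohort mostly non-ICU. That is a fair inference, but no ICU share is stated, and ICU patients who were not invasively ventilated remain eligible.

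**Conclusion.** The point holds as one of calibration and labelling. A threshold described as presumable is moved unchanged to a reworded scale and a different population, called diagnostic, and left without a reference standard or a stated limitation. The resulting proportion is a screen-positive rate whose error has unknown direction and may be large: 3.8% to 14.6% for a true 5.8% under the assumed pairs. That it cannot be read as PTSD frequency rests on the article's text alone. The size rests on the assumed sensitivities, specificities and prevalences. The reach is limited to a secondary outcome and to any analysis that uses the yes/no split. The primary question on fatigue with depression or anxiety is untouched.

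**What to change.** - In PTSD Assessment, delete the word diagnostic. Report the proportion as screen-positive at the threshold taken from the original ICU-worded scale, and state whether the rule is above 45 or at least 45.
- Name the continuous PTSS-14 total, through the correlation already listed in phase 2.2.1(4), as the main analysis for research question 3.
- In phase 5, compare the continuous PTSS-14 score across the phase 3 groups in place of a chi-square test on the split at 45.
- In Limitations, say that neither the adapted wording nor the threshold has been validated in patients with COVID-19.
- Optionally, show the screen-positive proportion by ICU admission, but only if admission is recorded as its own item. The critical severity category pools it with high-flow oxygen, septic shock and other organ failure, so that category alone cannot supply the split.

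This needs no new patients or measurements, only wording and a change of one test. The price is a weaker claim about prevalence.
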